### Analysis of secondary outcomes

#### CPG disability at 6 months

This outcome will be analysed using the same methods as CPG disability at 12 months.

#### CPG pain intensity, HADS Anxiety, HADS Depression, and HEIQ at 6 and 12 months

These outcomes will be analysed using the same methods as CPG disability at 6 and 12 months.

#### PSEQ at 6 and 12 months

These outcomes will be analysed using the same methods as CPG disability at 6 and 12 months, except the individual components of the PSEQ score at 12 weeks will also be included in the imputation model (in addition to the PSEQ score at baseline, 6, and 12 months).

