#### Secondary outcomes

The secondary outcomes are:

1. CPG disability at 6 months post-randomisation [3]

2. CPG pain intensity score at 6 and 12 months post-randomisation [3]

3. Pain Self-Efficacy Questionnaire (PSEQ) score at 6 and 12 months post-randomisation [4]

4. Hospital Anxiety and Depression Scale (HADS) Anxiety score at 6 and 12 months post-randomisation [5]

5. Hospital Anxiety and Depression Scale (HADS) Depression score at 6 and 12 months post-randomisation [5]

6. Chronic Pain Acceptance Questionnaire (CPAQ) score at 6 and 12 months post-randomisation [6]

7. Health Education Impact Questionnaire (HEIQ) Social integration score at 6 and 12 months post-randomisation [7]

8. EQ-5D at 6 and 12 months post-randomisation [8]

9. Census global health question at 6 and 12 months post-randomisation [9]

10. Total Defined Daily Doses (Total DDD) of psychotropic drugs consumed up to 12 months post-randomisation

11. Total DDD of analgesics (including all opioids and other central nervous system drugs) consumed for pain up to 12 months post-randomisation

12. Total DDD of weak opioids consumed up to 12 months post-randomisation

13. Total DDD of strong opioids consumed up to 12 months post-randomisation

14. Proportion of participants using weak opioids at 12 months post-randomisation (defined as having received a prescription for a weak opioid up to twelve weeks before the 12-month follow-up date)

15. Proportion of participants using strong opioids at 12 months post-randomisation (defined as having received a prescription for a strong opioid up to twelve weeks before the 12-month follow-up date)

A guide to how outcomes are derived is available in Additional file 1.

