### Analysis principles

#### General analysis principles

The main analysis for each outcome will use intention-to-treat (ITT) principles, meaning that all participants with a recorded outcome will be included in the analysis, and will be analysed according to the treatment group to which they were randomised [10]. More information on which participants will be included in each analysis is available in later sections. All *P* values will be two sided, and the significance level is set at 5%.

Analyses for all outcomes will be presented as:

1. The number of participants included in the analysis, by treatment group;

2. A summary measure of the outcome, by treatment group (for example, mean (SD) for continuous outcomes, number (%) for binary outcomes). Only participants with a completely recorded outcome will be used to calculate the summary measure (for example, participants who complete only one of three components of the CPG disability score will not be included in the calculation of the summary measure, although they will be included in estimated the treatment through the use of multiple imputation - see later sections);

3. A treatment effect, with a 95% confidence interval;

4. A two-sided *P* value.

All analyses will account for clustering by course in the intervention group. This is because when the intervention is delivered in clusters (for example, in a group setting, or when the same therapist treats multiple patients) it is necessary to account for the clustering in the analysis to avoid increasing the type I error rate [11-13]. Participants in the control group (who do not attend courses), will act as their own cluster (that is, each participant in the control group will belong to a 'course’ where they are the only member).

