### Analysis of primary outcome

The primary outcome (CPG disability at 12 months) will be analysed using a mixed-effects linear regression model, with a 'group-based learning course’ as a random effect. Restricted maximum likelihood (REML) will be used. The model will include site of recruitment, age, gender, HADS depression score, and CPG disability at baseline as covariates.

All participants who completed at least one of the three questions that form the CPG disability score at either 6 or 12 months will be included in the analysis. Participants who did not fill out any portion of the CPG disability score at both 6 or 12 months will be excluded from the analysis.

Multiple imputation (MI) [28] will be used to account for participants who have an observed outcome at 6 months, but are missing the outcome at 12 months, as well as for participants who completed some, but not all, of the questions on the CPG disability score at 12 months. A total of 20 imputations will be performed, and results will be combined using Rubin’s Rules [28]. Only participants included in the analysis will be included in the imputation model. The imputation model will include the three questions that form the CPG disability score at baseline, 6 months, and 12 months, as well as the site of recruitment, age, gender, the HADS depression score at baseline, and employment status (employed or in full-time education versus not employed or in full-time education) (14 variables in total). We chose to include these variables in the imputation model because they will be included in the analysis model (CPG disability score at baseline, 6 months, and 12 months, site of recruitment, age, gender, and HADS depression score at baseline) or because we felt they may be predictive of missingness (employed or in full-time education versus not employed or in full-time education). Imputation will be performed separately within each treatment group [29]. In the intervention group, multilevel imputation will be performed, with 'course’ included in the imputation model as a random effect [30,31].

Missing data in any of the covariates to be adjusted for in the analysis (site of recruitment, age, gender, HADS depression score, CPG disability and baseline) will be accounted for at the same time as missing data in the CPG disability score at 6 or 12 months, as these variables will be included in the same imputation model.

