#### Participants with no completed follow-ups

The primary analysis has assumed that the excluded participants (those not completing any questions on the CPG disability questionnaire at both 6 and 12 months) were missing-at-random (that is, they were missing based on the covariates included in the analysis model). To assess the robustness to departures from this assumption, the primary outcome will be assessed under a range of missing-not-at-random scenarios. This will be done using the formula

$$\Delta =\Delta_{\mathrm{primary}}+Y_{1}P_{1}-Y_{2}P_{2}$$

where ∆ is the treatment effect under the missing-not-at-random scenario, ∆_primary_ is the treatment effect from the primary analysis, Y_1_ and Y_2_ are the assumed mean responses for participants with missing data in treatment groups 1 and 2 respectively, and P_1_ and P_2_ are the proportion of participants who were excluded from the analysis in groups 1 and 2, respectively. The standard error for ∆ is assumed to be approximately equal to the standard error for ∆_primary._ Y_2_ will be varied between 10, 25, 50, 75, and 90, and for each value of Y_2_, Y_1_ will be set to Y_2_ - 10, Y_2_, and Y_2_ + 10. For example, for Y_2_ = 25, Y_1_ will vary between 15, 25, and 35.

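### PSEQ: participants who answered only at 12 weeks are left out of both analysis and imputation, although the 12-week items are in the imputation model

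*SAP article*

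**What the plan says.** In the SAP article, *PSEQ at 6 and 12 months* points back to the CPG disability methods and makes one change: "except the individual components of the PSEQ score at 12 weeks will also be included in the imputation model". It says nothing about who enters the analysis.

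The inherited rules are in *Analysis of primary outcome*, and *CPG disability at 6 months* carries them to the earlier time point:

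- Entry, in a sentence that goes on to admit these people to the analysis: "All participants who completed at least one of the three questions that form the CPG disability score at either 6 or 12 months will be".
- Exclusion: "Participants who did not fill out any portion of the CPG disability score at both 6 or 12 months will be excluded from the analysis".
- Imputation set: "Only participants included in the analysis will be included in the imputation model".

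Two further statements bear on the point. *Secondary outcomes* lists the "Pain Self-Efficacy Questionnaire (PSEQ) score at 6 and 12 months post-randomisation" and no 12-week PSEQ outcome. *General analysis principles* defines intention to treat so that "all participants with a recorded outcome will be included in the analysis".

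**The concern.** The primary analysis lets an earlier follow-up stand in for a missing later one: a participant with 6-month data only is kept and the 12-month value is imputed. For CPG disability the imputation model holds no follow-up other than 6 and 12 months, so the entry rule admits everyone with follow-up data in that model. PSEQ has a further follow-up at 12 weeks, and the imputation model was extended to use it. The entry rule was not extended with it. The 12-week items therefore help to impute only for people who also answered at 6 or 12 months.

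What is at stake is the missing-data assumption. For participants excluded from the primary analysis, *Participants with no completed follow-ups* assumes that "they were missing based on the covariates included in the analysis model", and those covariates are all measured at or before baseline. Carried over to PSEQ, the same assumption sets aside an observed post-randomisation value of the same scale. If people with low 12-week self-efficacy drop out afterwards, and do so at different rates in the two arms of this unmasked trial, the PSEQ effect is shifted. The missing-not-at-random check in that section is written for the primary outcome only, so nothing in the article examines this for PSEQ.

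**Working it through.** **Rule trace.** The entry rule is worded for the CPG questions. Its natural translation is at least one PSEQ item at 6 or 12 months, and the EQ-5D and Census sections restate the same two-visit window in their own terms. Take a participant with PSEQ at 12 weeks and nothing later. The entry rule is not met, so the participant is not analysed. Imputation is confined to analysed participants, so the participant is not imputed either. The single PSEQ exception adds variables to the imputation model, not people.

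**Size.** The plan states no figure to reproduce: it gives no count of 12-week-only participants, no PSEQ SD, no correlation and no dropout pattern. What follows rests on assumed values.

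Inputs:
- f, the share of an arm with 12-week PSEQ only: 2% to 10% (assumed)
- r, the correlation of 12-week with 12-month PSEQ given covariates: 0.4 to 0.8 (assumed)
- d, the 12-week gap between retained and excluded participants, in covariate-adjusted SD: 0.25 to 1 (assumed)
- numbers randomised: 403 and 300 (SAP article, *Background*)

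*Precision.* The ratio of standard errors, included over excluded, is √[(1 − r²) + r²(1 − f)] = √(1 − r²f).
- f = 0.02, r = 0.4: √(1 − 0.0032) = 0.998
- f = 0.10, r = 0.8: √(1 − 0.064) = 0.967

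The reduction is about 0.2% to 3.3%.

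*Shift in one arm's mean from exclusion.* This is f × r × d.
- Smallest: 0.02 × 0.4 × 0.25 = 0.002 SD
- Largest: 0.10 × 0.8 × 1 = 0.08 SD

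Only the difference between arms reaches the treatment effect. With equal f, r and d it cancels.

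*Differential loss, 8% against 4%.* The shift in the effect is (0.08 − 0.04) × r × d = 0.04 × r × d.
- r × d = 0.4 × 0.25 = 0.1: 0.004 SD
- r × d = 0.8 × 1 = 0.8: 0.032 SD

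The standard error of the effect in the same SD units, before attrition and clustering, is √(1/403 + 1/300) = 0.076. The shift is then 0.004/0.076 = 0.05 to 0.032/0.076 = 0.42 of a standard error.

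In points, take an assumed PSEQ SD of 13 and a baseline correlation of 0.6 to 0.7. The adjusted SD is 13 × √(1 − 0.36) = 10.4 to 13 × √(1 − 0.49) = 9.3. The standard error is then 0.79 to 0.71 points, and the shift runs from 0.004 × 9.3 = 0.04 to 0.032 × 10.4 = 0.33 points.

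*Simulation.* Large-sample simulation with an assumed SD of 13, a true effect of about 1.6 points and dropout driven by 12-week PSEQ falls within that range:

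| Loss, intervention/control | Excluded | Included |
|---|---|---|
| 5% / 5% | 1.60 | 1.59 |
| 8% / 4% | 1.85 | 1.65 |
| 4% / 8% | 1.41 | 1.61 |
| 10% / 5% | 1.89 | 1.64 |

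Against 1.6, exclusion shifts the estimate by 0.25 points at 8%/4%, by 0.19 at 4%/8% and by 0.29 at 10%/5%. With r of 0.4 to 0.6 and weaker dependence of dropout on 12-week PSEQ, the shift at 8%/4% or 4%/8% was 0.05 to 0.15 points. All of these are well under one standard error.

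**The case against.** The strongest reply is that no stated rule is broken. A reader might infer that the plan promises to analyse anyone with any item at any follow-up, and then breaks that promise for PSEQ. The documents do not support this. The entry window is 6 or 12 months for every questionnaire outcome, the listed PSEQ outcomes are at those times only, and intention to treat is tied to a recorded outcome. Nor does being an imputation variable make a person eligible: employment status and the baseline items are in the model and admit nobody. The 12-week items are not wasted either, since they still improve imputation for those with some later data. All of this stands.

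It can also be said that every outcome value analysed for a 12-week-only participant would be imputed. That is true, but the plan already imputes the 12-month value for people seen only at 6 months, and 12-week PSEQ is likewise an earlier measurement of the same scale.

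The reply is strong on size as well. The 8%/4% case needs about 32 of 403 and 12 of 300 participants who answered at 12 weeks and never again. The subgroup may be far smaller, and nothing shows that loss differed between arms or depended on 12-week PSEQ. The simulation imputed whole scores by arm-specific regression. The plan imputes items, multilevel by course in the intervention arm, with 20 imputations, so full removal of the bias by inclusion is not shown for the planned method. These limits hold. They bear on severity and leave the rule trace intact.

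**Conclusion.** The point holds as a low-severity improvement. As written, participants with PSEQ at 12 weeks only are left out of both the analysis and the imputation, and the plan loses observed data that its own model was extended to use. Admitting them would relax the missing-at-random assumption for this group from baseline covariates alone to baseline covariates plus observed 12-week PSEQ.

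Under assumed values, the bias is negligible with equal loss. It is about 0.05 to 0.25 points with 8% against 4% loss that depends on 12-week PSEQ, and the gain in precision is 0.2% to 3.3%. Heavier loss or stronger dependence gives somewhat more, still under one standard error.

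A reader might go further and conclude that the PSEQ effect is biased by 12% to 15%. That figure is 0.19/1.6 to 0.25/1.6: it divides a shift from chosen adverse cases by an assumed effect, and the documents support neither number. The primary outcome is not affected.

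**What to change.** In *PSEQ at 6 and 12 months*, add one sentence: every participant with one or more PSEQ items answered at 12 weeks, 6 months or 12 months enters both the PSEQ analysis and its imputation model. Leave the analysis model as it is, and report by arm how many participants have 12-week PSEQ only. If the narrower set is preferred, state the reason and still report that number.

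The cost is one sentence, with no new data and no new model. The change adds participants to the imputation and no variables, so it does not worsen the problem of many item variables that the plan raises for CPAQ. The downside is that slightly more 6- and 12-month PSEQ values are imputed.

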#### CPAQ at 6 and 12 months

These outcomes will be analysed using the same methods as CPG disability at 6 and 12 months, with the exception of how CPAQ at baseline is included in the MI model. We will include the individual questions for CPAQ at 6 and 12 months in the imputation model, and include the overall CPAQ score at baseline For participants who are missing CPAQ at baseline, we will use mean imputation [33]. We chose this approach because CPAQ is a composite of 20 questions including each of these questions at each time point in the imputation model would lead to 60 variables being included (20 questions at baseline, 20 at 6 months, and 20 at 12 months), which may cause problems [34]. Including the overall CPAQ score at baseline rather than the 20 individual questions would reduce the number of variables from 60 to 41.

#### EQ-5D at 6 and 12 months

These outcomes will be analysed using the same analysis model as the primary outcome (that is, a mixed-effects linear regression model, with course as a random effect, adjusted for site of recruitment, age, gender, HADS depression score, and EQ-5D at baseline).

All participants who fully complete the EQ-5D score at either 6 or 12 months will be included in the analysis.

MI will be used to account for participants who are missing the outcome at either 6 or 12 months. The MI strategy will be the same as that for the primary and other secondary outcomes, except instead of imputing the individual components of the EQ-5D score, we will impute the whole score.

#### Census global health question at 6 and 12 months

These outcomes will be analysed using a mixed-effects ordered logistic regression model, with 'course’ as a random effect. Site of recruitment, age, gender, HADS depression score, and the outcome at baseline will be included as fixed covariates.

All participants who completed the Census global health question score at either 6 or 12 months will be included in the analysis.

MI will be used to account for participants who are missing the outcome at either 6 or 12 months. The MI strategy will be the same as that for the primary and other secondary outcomes, except we will impute the whole score (as there are no individual components).

#### Total DDDs up to 12 months post-randomisation for psychotropic drugs, drugs for pain, weak opioids, and strong opioids

These outcomes will be analysed using a mixed-effects linear regression model, with 'course’ as a random effect. Restricted maximum likelihood (REML) will be used. The model will include site of recruitment, age, gender, HADS depression score, and Total DDD in 3 months before randomisation at baseline as covariates. All participants who have data on Total DDD up to 12 months post-randomisation will be included in the analysis. In order to include participants with missing covariates in the analysis, mean imputation will be used to account for missing baseline covariates [33].

#### Proportion of participants using weak opioids and strong opioids at 12 months post-randomisation

These outcomes will be analysed using a mixed-effects logistic regression model, with 'course’ as a random effect. The model will include site of recruitment, age, gender, HADS depression score, and weak or strong (depending on outcome) opioid use at baseline (defined as a prescription for weak or strong) opioids in the 12 weeks before randomization) as covariates. All participants who have data on whether they had had a weak/strong opioid prescription at 12 months will be included in the analysis. Mean imputation will be used to account for missing baseline covariates [33].

### Adherence-adjusted analysis

As a secondary analysis, CPG disability, CPG pain intensity, PSEQ, HADS anxiety, HADS depression, CPAQ, HEIQ, and EQ-5D, all at 12 months will be re-analysed to obtain a complier average causal effect of treatment (CACE) [35,36]. This is because while ITT will give an unbiased estimate of the effect of assigning treatment, it may underestimate the effect of actually receiving the treatment. An analysis using CACE will lead to an unbiased estimate of receiving treatment.

We define 'compliers’ as those who attend more than half of the course (that is, those present for at least 12 of the 24 course components). The compliers can only be observed in the intervention group, where an indicator variable will indentify whether the individual complied. The compliers’ class is unobserved in the control group.

The analysis will be performed using the Stata command ivregress, with the option vce (cluster *clustvar*) to account for clustering by course group. Randomisation will be used as an instrumental variable for treatment received. The main analysis will be adjusted for CPG disability score at baseline, site of recruitment, age, gender, and the HADS depression score at baseline. Analyses will be performed using the same multiply imputed datasets as the primary analysis. The assumptions used for this analysis, as well as other adherence-adjusted analyses to be performed, are listed in the online appendix.

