Site of recruitment (London or Midlands) [14-17], age, gender, and the HADS depression score at baseline will be included as covariates in each analysis [17-20]. Additionally, for continuous outcomes (CPG disability, CPG pain intensity, PSEQ, HADS Anxiety, HADS Depression, CPAQ, HEIQ, and EQ-5D), the outcome measured at baseline will be included in the analysis [19]. Site of recruitment will be adjusted for because it was used as a stratification factor in the randomisation process, and therefore, it is necessary to include it in the analysis to maintain correct type I error rates [11,14-16]. The other covariates will be included in the analysis because adjustment for prognostic factors can substantially increase power [17-21].

Continuous covariates (age, HADS depression score, outcome measured at baseline) will be analysed using a linear relationship with the outcome, as categorising continuous covariates has been shown to lead to poor performance in other scenarios [22]. We made the decision to assume a linear relationship prior to examining the observed association between covariate and outcome in the trial data, as previous research has shown that choosing the analysis method based on study data can lead to biased treatment effect estimates and incorrect type I error rates in some scenarios [23-27].

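### As written, the complier-effect analyses of eight outcomes share one baseline covariate and one set of imputed datasets, both of which belong to CPG disability.

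*SAP article*

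**What the plan says.** The Adherence-adjusted analysis section sets the scope: "CPG disability, CPG pain intensity, PSEQ, HADS anxiety, HADS depression, CPAQ, HEIQ, and EQ-5D, all at 12 months will be re-analysed". It then gives a single adjustment set, "The main analysis will be adjusted for CPG disability score at baseline, site of recruitment, age, gender, and the HADS depression score at baseline", and a single data source, "Analyses will be performed using the same multiply imputed datasets as the primary analysis". Neither sentence says that the outcome concerned is to be substituted.

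Three other parts of the SAP article bear on this:

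- **General analysis principles.** For continuous outcomes, "the outcome measured at baseline will be included in the analysis". The list there names the same eight outcomes.
- **Analysis of primary outcome.** "The imputation model will include the three questions that form the CPG disability score at baseline, 6 months, and 12 months". Site, age, gender, baseline HADS depression and employment status are added, giving "14 variables in total". On who is covered: "Only participants included in the analysis will be included in the imputation model". That means participants who answered at least one CPG disability question at 6 or 12 months.
- **Analysis of secondary outcomes.** Each of the other seven outcomes has its own imputation, by reference to the primary method or with stated changes. EQ-5D, for example, has its own inclusion rule and is imputed as a whole score.

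**The concern.** The CACE section reads as if written for CPG disability and then extended to seven more outcomes without adapting two sentences. An analyst who follows it literally would adjust PSEQ, CPAQ or EQ-5D for baseline CPG disability and not for its own baseline. The same analyst would look for imputed 12-month values in datasets that were not built to hold them.

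The section justifies CACE by contrast with ITT, which it says may understate the effect of receiving the treatment. That contrast is easiest to read when both estimates rest on the same participants, imputations and covariates. If they do not, a gap between CACE and ITT for, say, PSEQ mixes the effect of non-adherence with differences in population, missing-data handling and adjustment.

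**Working it through.** **1. Reproduce the stated count.** The inputs are in Analysis of primary outcome.

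- CPG disability items: 3 questions × 3 time points = 9.
- Others: site, age, gender, baseline HADS depression, employment = 5.
- Total: 9 + 5 = 14, which matches the stated total. No place is left for another outcome.

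**2. Set the eight CACE outcomes against the two sentences.**

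| Outcome at 12 months | Own baseline in the stated covariates? | 12-month value in the 14 variables? |
|---|---|---|
| CPG disability | yes | yes (as items) |
| HADS depression | yes | no |
| CPG pain intensity | no | no |
| PSEQ | no | no |
| HADS anxiety | no | no |
| CPAQ | no | no |
| HEIQ | no | no |
| EQ-5D | no | no |

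So 8 − 2 = 6 outcomes lack their own baseline, and 8 − 1 = 7 have no imputed 12-month value.

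**3. What this means for participants, using EQ-5D.** Its ITT analysis takes everyone who fully completed EQ-5D at 6 or 12 months and imputes the missing score.

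- Someone with EQ-5D at 6 months only, and at least one CPG disability item, is in the primary datasets but has no imputed 12-month EQ-5D there.
- Someone with a complete EQ-5D but no CPG disability item at either time is in the EQ-5D ITT analysis and absent from the primary datasets.

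**4. Size of the covariate point.** The document gives no correlations, so these are assumptions: an outcome correlates r_own = 0.60 to 0.70 with its own baseline and r_CPG = 0.30 to 0.45 with baseline CPG disability. Taking the SE as proportional to the residual SD, and ignoring the other covariates:

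SE ratio = √[(1 − r_CPG²) / (1 − r_own²)]

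Sample equivalent = 1 − 1/ratio²

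| r_own | r_CPG | Variance ratio | SE ratio | Sample equivalent |
|---|---|---|---|---|
| 0.60 | 0.45 | 0.7975 / 0.64 = 1.246 | 1.12 | 20% |
| 0.60 | 0.30 | 0.91 / 0.64 = 1.422 | 1.19 | 30% |
| 0.70 | 0.45 | 0.7975 / 0.51 = 1.564 | 1.25 | 36% |
| 0.70 | 0.30 | 0.91 / 0.51 = 1.784 | 1.34 | 44% |

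Over the whole assumed range the SE is about 12% to 34% larger, like losing about 20% to 44% of the sample.

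**The case against.** The best defence is that this is condensed drafting. Elsewhere the article treats sameness with the primary outcome as the same method with the outcome swapped in. General analysis principles already requires own-baseline adjustment for these eight outcomes, and outcome-specific imputations are already planned. On that view the covariate sentence illustrates CPG disability, and the dataset sentence means each outcome's own main analysis.

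This is plausible as intent, but the text does not say it. The sensitivity-analysis sections use the term primary analysis for the analysis of the primary outcome. Where the article means a substituted baseline it can name it, as it does for EQ-5D. If both sentences cover CPG disability only, the section names no datasets for the other seven outcomes, and an edit is still needed. The online appendix is not shown and may hold more detail. The article cites it for assumptions and for other adherence-adjusted analyses, not for these covariates or datasets, so it lowers certainty only a little.

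Three limits on the concern do stand:

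- Baseline HADS depression is in the covariate set, so HADS depression is adjusted for its own baseline.
- CPG pain intensity belongs to the same questionnaire as CPG disability, so it would be wrong to say that all seven outcomes are analysed in a set defined by a different instrument.
- Baseline HADS depression may already explain part of the variation in outcomes such as HADS anxiety, PSEQ or CPAQ, so the precision loss could be smaller than the illustration.

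**Conclusion.** The point holds as an internal contradiction in a secondary analysis. Six outcomes are not adjusted for their own baseline, against the plan's general rule. For seven, the dataset instruction cannot be carried out as specified, or it yields a CACE whose population and missing-data handling differ from those of the matching ITT analysis. The dataset sentence is the more serious of the two.

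These counts come from the document alone. The 12% to 34% increase in SE does not: it rests on assumed correlations and leaves out the shared covariates.

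A reader might infer three stronger things that the document does not support:

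- **That the seven outcomes are to be analysed without imputation.** This is a likely result of following the text, but the plan does not prescribe it; it calls for multiply imputed datasets.
- **That the CACE estimates are biased by the wrong baseline covariate.** Randomisation is the instrument, so the covariate choice costs precision and comparability and does not in itself cause bias.
- **That the primary or secondary ITT results are affected.** They are specified separately, and nothing here touches them.

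**What to change.** Replace the two sentences in the Adherence-adjusted analysis section with wording to this effect:

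*Each CACE analysis will adjust for that outcome's own baseline value, site, age, gender and baseline HADS depression, and will use the multiply imputed datasets created for that outcome's own ITT analysis.*

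For HADS depression, the own baseline and the common covariate are the same variable and enter once. The cost is a short text edit. No new imputation is needed, because the outcome-specific datasets are already planned, and no stated figure in the plan changes.
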